## Abstract

**Background:**

WHO recommends that HIV infected women receive antiretroviral therapy (ART) minimally during pregnancy and breastfeeding (“Option B”), or ideally throughout their lives regardless of clinical stage (“Option B+”) (Coovadia et al., Lancet 379:221–228, 2012). Although these recommendations were based on clinical trials demonstrating the efficacy of ART during pregnancy and breastfeeding, the population-level effectiveness of Option B+ is unknown, as are retention on ART beyond the immediate post-partum period, and the relative impact and cost-effectiveness of Option B+ compared to Option A (Centers for Disease Control and Prevention, Morb Mortal Wkly Rep 62:148–151, 2013; Ahmed et al., Curr Opin HIV AIDS 8:473–488, 2013). To address these issues, we conducted an impact evaluation of Zimbabwe’s prevention of mother to child transmission programme conducted between 2011 and 2018 using serial, community-based cross-sectional serosurveys, which spanned changes in WHO recommendations. Here we describe the rationale for the design and analysis.

**Methods/design:**

Our method is to survey mother-infant pairs residing in the catchment areas of 157 health facilities randomly selected from 5 of 10 provinces in Zimbabwe. We collect questionnaires, blood samples from mothers and babies for HIV antibody and viral load testing, and verbal autopsies for deceased mothers/babies. Using this approach, we collected data from two previous time points: 2012 (pre-Option A standard of care), 2014 (post-Option A / pre-Option B+) and will collect a third round of data in 2017–18 (post Option B+ implementation) to monitor population-level trends in mother-to-child transmission of HIV (MTCT) and HIV-free infant survival. In addition, we will collect detailed information on facility level factors that may influence service delivery and costs.

**Discussion:**

Although the efficacy of antiretroviral therapy (ART) during pregnancy and breastfeeding for prevention of mother-to-child transmission of HIV (PMTCT) has been well-documented in randomized trials, little evidence exists on the population-level impact and cost-effectiveness of Option B+ or the influence of the facility on implementation (Siegfried et al., Cochrane Libr 7:CD003510, 2017). This study will provide essential data on these gaps and will provide estimates on retention in care among Option B+ clients after the breastfeeding period.

**Trial registration:**

NCT03388398 Retrospectively registered January 3, 2018.

## Background

Despite the implementation of increasingly efficacious drug regimens for the prevention of mother-to-child HIV transmission (PMTCT), in 2016,160,000 children became infected with HIV worldwide, of whom 48% lived in eastern and southern Africa [1]. Most pediatric HIV infections are acquired through mother-to-child transmission (MTCT), which can occur during pregnancy, delivery or breastfeeding [2]. In the absence of antiretroviral prophylaxis (ARV) or antiretroviral therapy (ART), MTCT ranges between 15 and 45% [3]. While the use and efficacy of ART during pregnancy and breastfeeding for PMTCT under controlled circumstances has been well documented [4, 5], the population-level effectiveness in real-world conditions has not [6].

Following the 2010 revision of the WHO PMTCT guidelines for resource-poor settings [7, 8] and the 2011 UNAIDS plan to eliminate MTCT globally [6], scale-up efforts for PMTCT interventions were renewed and highly efficacious ARV prophylaxis regimens became available in many low-income countries (e.g., Option A). Compared to earlier guidelines, Option A of the 2010 WHO guidelines recommended lifelong ART for a larger group of HIV-infected women (i.e., CD4 ≤ 350 or clinical stage 3–4 vs. CD4 ≤ 200), and that ARV prophylaxis be provided earlier in the pregnancy (i.e., starting at 14 weeks instead of 28) [9]. The commitment to scale up PMTCT interventions was further renewed in 2013 when the WHO released updated guidelines recommending that all pregnant women receive antiretroviral therapy throughout their lives regardless of clinical stage (Option B+) [10, 11]. However, MTCT rates in low resource settings remain higher than the levels achieved in efficacy studies [12, 13] or better-resourced settings, reflecting the reality that PMTCT effectiveness is a function of *both* ART efficacy *and* the proportion of HIV-infected pregnant women engaged and retained in PMTCT services [14]. In addition to accelerating the scale-up of PMTCT services, UNAIDS and WHO have urged countries to conduct population-level impact evaluations of their PMTCT programs [6, 15] to assess the extent to which these programs avert pediatric infections and to monitor progress towards PMTCT elimination goals [14, 15]. Despite the current global call for PMTCT effectiveness studies in developing countries, few countries have so far assessed the population-level impact of their PMTCT interventions [16, 17]. Equally unknown is the cost-effectiveness of PMTCT interventions such as Option B+, which remains a critical pending question in the context of limited resources for HIV programming.

In Zimbabwe, eliminating MTCT poses a formidable public health challenge. An estimated 1.3 million people are living with HIV, with an estimated 4900 new HIV infections in children each year [18]. In 2011, Zimbabwe’s Ministry of Health and Child Care (MOHCC), intensified the existing PMTCT program and scaled up a nationwide program to accelerate the elimination of pediatric HIV/AIDS. Reaching 60 of 62 districts and approximately 1560 health facilities, MoHCC supported the implementation of Option A of the 2010 WHO guidelines, distributed point-of-care CD4 testing machines for determination of ART eligibility, and facilitated community mobilization to increase entry and retention in the PMTCT cascade. In November 2013, the MOHCC updated its guidance to Option B+ as recommended in the 2013 WHO guidelines.

The scale-up of the accelerated PMTCT program in Zimbabwe provides an opportunity to ascertain the effectiveness of PMTCT programs at a national level. We will combine three rounds of serial community-based cross-sectional serosurveys to evaluate the population-level impact of Option B+ in Zimbabwe. Our 2017–2018 endline serosurvey (post Option B+) will be combined with data from our previous serosurveys conducted in 2012 (pre-Option A standard of care) and 2014 (post-Option A/pre-Option B+). These three surveys will allow us to monitor population-level trends in MTCT and HIV-free infant survival over the previous 6 years and to assess the impact of Option B+ compared to i) pre Option A and ii) post Option A pre Option B+. We use a population-based approach, as estimates from facility-based studies by definition will be less likely to include women who do not attend clinics for antenatal care and delivery. As with many settings in sub-Saharan Africa, mobility and migration are also a concern in assessing outcomes as many women may move during the postpartum period and become lost or be considered lost to care from a facility when they change care locations. Our study design allows us to assess HIV-free infant survival and MTCT at a community level at 9–18 months postpartum, thus taking into account HIV transmissions occurring during pregnancy, labor and delivery and breastfeeding among both women who access PMTCT services and those that do not [17]. We will specifically collect information on antenatal care attendance and facility based delivery as well as changes in care location and gaps in care related to mobility/migration.

In addition to evaluating the impact of Option B+, we will collect facility level data to explore impact heterogeneity and cost-effectiveness by facility and community level factors (e.g. MTCT) allowing us to assess Option B+ cost-effectiveness compared to Option A. Finally, our endline survey will include a population-based assessment of retention in HIV care long enough for some mothers who received Option B+ to have weaned their infant thus permitting an evaluation of care beyond the post-partum period. Here we describe our methodological approach for this impact evaluation.

## Methods/design

### Specific objectives

The specific objectives of this study include:Objective 1a, 1b: Compare the population-level impact of Option B+ on HIV-free survival and MTCT among infants 9–18 months of age in Zimbabwe to: a) standard of care before Option A; and b) Option A.Objective 2: Use facility and community level data to assess heterogeneity of the impact of Option B+ on HIV-free survival and MTCT among infants 9–18 months of age by the extent of integration of PMTCT and ART services at health facilities, among other factors.Objective 3: Assess retention of mothers in ART services 19–36 months postpartum.Objective 4a, 4b: Determine the cost-effectiveness of Option B+ compared to: a) the standard of care before Option A; and b) Option A.

### Study site and population

A timeline of data collection activities for the three cross-sectional serosurveys is summarized in Fig. 1. The study population consists of infants born 9–18 months prior to the surveys (alive or deceased) and their mothers or caregivers (at least 16 years old) living in the catchment areas of 157 randomly selected health facilities in five of Zimbabwe’s ten provinces. The five provinces (Harare, Mashonaland West, Mashonaland Central, Manicaland, and Matabeleland South) were selected in 2012 to include three of the four largest cities in Zimbabwe, rural communities with high and low HIV prevalence, and both major ethnic groups in Zimbabwe (i.e. Shona, Ndebele). The 2017–18 survey will include an additional sample of mothers at least 16 years old who have infants 19–36 months of age in order to examine retention in care. Caregiver-infant pairs are enrolled even if the mother of an eligible child has died or has left the baby for a prolonged period of time (e.g., working elsewhere).

**Fig. 1 Fig1:**
[figure not shown]
Study Diagram

For facility-level surveys, the study population consists of healthcare staff at health facilities in the sampled communities in order to assess facility-level characteristics associated with MTCT (i.e. staff training, infrastructure), and the cost of delivering PMTCT services.

### Sampling strategy

In the first stage of our multi-stage sampling process, we selected catchment areas of health facilities offering PMTCT services within each district of five provinces of Zimbabwe as primary sampling units (PSUs), 157 of 699 catchment areas were randomly selected with probability proportionate to the number of facilities in each district. In 2012 and 2014, the second stage of sampling selected eligible mother-infant pairs living in the catchment areas of these 157 facilities. Women are considered eligible if they are at least 16 years old, able to respond to questions in English or Shona/Ndebele and are living in a catchment area household.

Eligible mother-infant pairs were selected using a pre-determined sampling fraction that was a function of the number of mother-infant pairs identified. In catchment areas with fewer eligible pairs, a greater proportion were sampled to ensure a minimum sample of 50 mother-infant pairs from each catchment area. During the first two survey rounds, eligible mother-infant pairs were identified based on information pooled from: 1) village health workers (VHWs) and 2) immunization registers from selected facilities and neighboring facilities (to identify women residing in sampled facilities who accessed services at adjacent facilities) [9]. Further, mothers identified using (1) and (2) were asked to identify other eligible infants in their neighborhood [9].

For the final survey round in 2017–2018 the investigators chose to adjust the second stage sampling. By this time, a cost-effective strategy engaging community health workers to conduct geographic mapping and to comprehensively identify eligible study participants had been demonstrated by other recent projects in Zimbabwe [19]. Although our previous three-pronged approach, pooling information from VHWs, immunization registers, and respondent driven sampling in each neighborhood, allowed efficient identification of eligible mother-infant pairs without screening all households in a selected CA, it may have systematically excluded eligible mother-infant pairs less likely to access health services. Hence, in discussions with the MOH, we chose to improve the rigor of our sampling procedures, i.e. enumerating catchment area populations by VHWs *prior* to data collection in order to permit more rigorous identification of all eligible study participants. In doing so, we also increase the utility of our findings for MOH efforts aimed at quantifying Zimbabwe’s progress toward elimination of MTCT.

In 2017–18, the second stage of sampling was adapted as follows. Rather than sampling mother infant pairs, we are sampling geographic areas demarcated by the Zimbabwe National Statistics Agency (ZIMSTAT) for use in the national census within each clinic catchment area. These units are referred to as enumeration areas or EAs, and each unit is expected to contain roughly 100 households.

Sampling fractions for EAs within each catchment area were chosen to target selection of roughly 50 mother-infant pairs per catchment area. Sampling fractions used in in the 2014 survey round to select eligible mother-infant pairs in each catchment area were used as a base to select a comparable proportion of EAs from each catchment area for the 2017–18 round. Adjustments were made to sampling fractions to mandate a minimum selection of 7 EAs per clinic catchment area, or all EAs if there were fewer than 7 EAs associated with a clinic catchment area. In each selected EA, village health workers (VHW) are trained by and work in conjunction with survey staff to conduct a full census of all households in the selected EAs. The VHWs and survey teams use area maps to visit all identified structures, and record the number of potentially eligible mothers and infants by visiting households and conducting a short screening survey to ascertain the presence of eligible mother/caregiver-infant pairs. Within the selected EAs, all eligible mothers who have given birth 9–18 months prior, and all infants 9–18 months old are selected for inclusion in the survey. We will also sample 10% of mothers 19–36 months postpartum in order to assess longer term engagement in care following the end of the breastfeeding period.

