### Statistical power

We hypothesized that differences in HIV-free infant survival and MTCT between Option B+ (2017 estimates) and the pre-Option A standard of care (2012 estimates) will be greater than the differences between Option B+ (2017–18 estimates) and Option A (2014 estimates). Therefore, sample size calculations for the community surveys were conducted targeting the comparison between 2014 and 2017–18 estimates, as described below.

Sample size calculations were based on the formula for unadjusted comparison of proportions within matched pairs (where a “pair” is two measurements of the outcome within the same catchment area e.g. MTCT in a given facility in 2014 and in 2017–18) [21]. Findings from the 2012 survey estimate an average ANC prevalence of 12.5% among mothers in our catchment areas, with 9% of HIV exposed 9–18 month old infants being infected and 10% of HIV-exposed infants being deceased or infected with HIV [9]. In 2014 ANC prevalence was 13.6% among mothers in our catchment areas and the proportion of HIV-exposed infants who were deceased or HIV-infected had dropped to 4.8% [22]. In Zimbabwe the national targets for Option B+ are 95% HIV-free infant survival and less than 5% MTCT. Consequently, we calculated the sample size needed to detect a reduction from 2014 outcome proportions to 3.4% HIV infection or death in 2017–18.

Based on our 2012 and 2014 survey experience, we presume the 2017–18 survey will have a survey refusal rate of 2% and a value of 0.25 for the coefficient of variation (k_m_). Using a two sided-test at a 5% level of significance and a desired power of 80%, we would require a harmonic mean greater than 4 HIV-exposed infants (i.e., infants whose mothers are HIV-infected) per catchment area. We expect that the prevailing trend of decreasing ANC prevalence will continue [23] and therefore assume that ANC prevalence will have decreased to 11.5% by 2017–18. Taking into account variability in both catchment area size and underlying HIV prevalence among pregnant women across PSUs (again, based on our 2012 and 2014 data) we estimate that we will need a sample 13,000 pairs in 2017–18. Using the above assumptions we would have 80% power to detect a difference in HIV-free infant survival between Option A and Option B+.

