For mothers at 19–36 months post partum, under the assumption of a 11.5% HIV prevalence among mothers in 2017–18, and taking into account variation in prevalence and refusal rates similar to those observed in the 2012 and 2014 surveys, we estimated that, in order to measure the proportion of mothers who continued ART after weaning, we would require a sample of approximately 1800 mother-infant pairs, of which approximately 200 mothers are expected to be HIV-infected.

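### The 2017–18 field target of about 50 pairs in each of 157 catchment areas (7,850 pairs) is about 40% below the 13,000 pairs stated as needed, and nothing in the article connects the two.

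*Protocol article*

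**What the plan says.** All references are to the protocol article.

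- **Sampling strategy, first stage:** "157 of 699 catchment areas were randomly selected".
- **Sampling strategy, 2012 and 2014:** smaller catchment areas were sampled more heavily, "to ensure a minimum sample of 50 mother-infant pairs from each catchment area". In those rounds 50 was a floor.
- **Sampling strategy, 2017–18:** the second stage selects EAs of about 100 households each. "Sampling fractions for EAs within each catchment area were chosen to target selection of roughly 50 mother-infant pairs per catchment area". The 2014 fractions served as the base and were then adjusted to "mandate a minimum selection of 7 EAs per clinic catchment area, or all EAs if there were fewer than 7 EAs". Within selected EAs, "all eligible mothers who have given birth 9–18 months prior, and all infants 9–18 months old are selected for inclusion in the survey". A further 10% of mothers at 19–36 months are sampled.
- **Statistical power, 9–18 months:** "we estimate that we will need a sample 13,000 pairs in 2017–18". This is tied to 80% power for the Option A versus Option B+ comparison (4.8% versus 3.4% dead or infected) and to a harmonic mean above 4 HIV-exposed infants per catchment area.
- **Statistical power, 19–36 months:** "we would require a sample of approximately 1800 mother-infant pairs, of which approximately 200 mothers are expected to be HIV-infected".

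**The concern.** The two sections describe the same 9–18-month sample for the same round, and their sizes do not agree. All eligible pairs in a selected EA are taken, so the EA sampling fraction, including its 7-EA floor, is the only stated design control on sample size. The only yield given for setting that fraction is about 50 pairs per area.

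If the field plan delivers what it aims at, the comparison that drove the sample size gets about three fifths of the planned 2017–18 data. If it delivers more, the article does not say how much more. Either way, the stated 80% power is attached to a sample that the stated sampling plan is not shown to produce.

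**Working it through.** **1. The plan's own figure.** The 13,000 cannot be recomputed, because the article does not give the between-area variability in size and prevalence that went into it. The check therefore compares the two stated figures.

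**2. Target against requirement.**
- Target: 157 × 50 = 7,850 pairs.
- Requirement per area: 13,000 / 157 = 82.8 pairs.
- Shortfall: 13,000 − 7,850 = 5,150, and 5,150 / 13,000 = 39.6%.
- If the 13,000 is read as including the 1,800 pairs at 19–36 months, 11,200 remain. That is 71.3 per area, and the gap is still 1 − 7,850 / 11,200 = 29.9%.

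**3. What the 7-EA floor would have to deliver.** With exactly 7 EAs in every area:
- 50 pairs per area needs 50 / 7 = 7.1 eligible pairs per EA.
- 13,000 pairs needs 82.8 / 7 = 11.8 eligible pairs per EA.

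The article gives about 100 households per EA but no eligible pairs per EA. It does not say which applies.

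**4. HIV-exposed infants** (11.5% prevalence and 2% refusal, both from Statistical power).
- 7,850 × 0.98 × 0.115 = 885, or 5.6 per area.
- 13,000 × 0.98 × 0.115 = 1,465, or 9.3 per area.

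**5. Effect on power, with 2014 held fixed.** The matched-pair cluster formula, with p0 = 0.048, p1 = 0.034, k_m = 0.25, c = 157, two-sided 5% and equal cluster sizes, is:

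Power = Φ( √[ (c − 2)(p0 − p1)² / V ] − 1.96 ), with V = p0(1 − p0)/m₂₀₁₄ + p1(1 − p1)/m₂₀₁₇ + k_m²(p0² + p1²).

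Here (c − 2)(p0 − p1)² = 155 × 0.000196 = 0.03038, p0(1 − p0) = 0.045696, p1(1 − p1) = 0.032844, and k_m²(p0² + p1²) = 0.000216. The 2014 number of exposed infants per area is not given, so three assumed values are shown:

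| Assumed m in 2014 | Power with 13,000 in 2017–18 (m = 9.33) | Power with 7,850 in 2017–18 (m = 5.64) | Loss (points) |
|---|---|---|---|
| 5.64 | 36% | 31% | 5 |
| 6.66 (50 pairs × 0.98 × 13.6%) | 39% | 34% | 6 |
| 9.33 | 47% | 38% | 8 |

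Worked cell, m = 9.33 in 2014 and 5.64 in 2017–18: V = 0.004897 + 0.005829 + 0.000216 = 0.010942; √(0.03038 / 0.010942) = 1.666; Φ(1.666 − 1.96) = 38%.

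**6. Cross-check from the 19–36-month sample.** The 1,800 does reproduce its own companion figure: 1,800 × 0.98 × 0.115 = 203 HIV-infected mothers. Assume births are spread evenly over 10 monthly ages (9–18) and 18 monthly ages (19–36).
- 1,800 at 10% means 18,000 mothers at 19–36 months, so 18,000 × 10 / 18 = 10,000 pairs at 9–18 months, or 64 per area.
- In the other direction, 7,850 pairs imply 7,850 × 1.8 × 10% = 1,413, and 13,000 pairs imply 2,340.

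The implied 10,000 matches neither stated figure.

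**The case against.** The best defence is that 50 is not the expected yield. The 2014 fractions are the base, and they were built around a minimum of 50. Where the 7-EA floor binds, it can only raise the sample, and every eligible pair is then taken.

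As an illustration on assumed inputs that are not in the article, take 4 to 5 persons per household and 25 to 35 births per 1,000 per year. An EA of 100 households then holds about 8.3 to 14.6 eligible pairs over a 10-month window (for example 100 × 4 × 0.025 × 10/12 = 8.3). Seven EAs would give 58 to 102 pairs, and the 11.8 per EA needed for 13,000 lies inside that range. Areas with fewer than 7 EAs would give less.

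This part stands: 7,850 is a stated target, not a forecast. A reader might infer that the survey will fall 40% short, and the article does not support that. Equally, it does not show that the floor closes the gap, and for 2017–18 it words 50 as the target, keeping the word minimum for the EA count.

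Three other stronger readings also go too far.
- **Power falling from 47% to 31%.** That contrast shrinks both rounds, but the 2014 data are already collected and cannot be changed by the 2017–18 target.
- **The harmonic-mean criterion fails at 7,850.** With assumed between-area coefficients of variation from 0 to 0.7, Poisson counts and zero-count areas dropped, 7,850 pairs give a harmonic mean of about 4.5 down to 3.3. The criterion may or may not be met.
- **The 19–36-month requirement is missed either way.** A yield of 2,340 would satisfy a requirement of 1,800, and the scaling rests on evenly spread births. It is supporting evidence only.

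**Conclusion.** The inconsistency is real and rests on direct arithmetic: the stated target is 7,850 pairs, the stated requirement is 13,000, and the difference is 39.6%. The text gives no pairs-per-EA figure or expected total to reconcile them. Whether the realised sample falls short cannot be judged from the article.

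If it did fall to 7,850, the cost in power would be about 5 to 8 percentage points. That figure assumes the matched-pair formula, equal clusters, the stated proportions, k_m, prevalence and refusal rate, and a 2014 size between 5.64 and 9.33 exposed infants per area.

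The power values in the table are below 80% even at 13,000, but this gap is not the reason. With the same formula and equal numbers in both rounds, 80% power needs about 21.5 exposed infants per area, where the article states a harmonic mean above 4. That is a separate problem and should not be charged to the mismatch discussed here. It does mean that 13,000 is the article's stated requirement and not a verified one.

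**What to change.** 1. State the number of eligible 9–18-month pairs assumed per EA, how often the 7-EA floor binds, how many areas have fewer than 7 EAs, and the expected total that follows. Say whether 50 is a target or a minimum in 2017–18.
2. Then do one of the following:
   - Recompute the EA fractions for areas not yet fielded so that the expected total is 13,000 (about 83 pairs per area).
   - Restate the expected sample (about 7,850 pairs and 885 HIV-exposed infants if 50 is the true target) and the power it gives, using the 2014 sample actually collected.
3. Check that the 10% fraction at 19–36 months still delivers about 1,800 mothers under the reconciled yield, and adjust the fraction or the stated figure if it does not.

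**Cost.** The restatement costs a few sentences and a less favourable figure. Recomputing fractions means extra EAs to census and survey, and it is possible only where fielding has not begun. The article describes the fractions as already chosen, so that option may be limited.

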## Data sources

### Community mapping for the endline survey

At the endline survey, prior to conducting the community census, the survey staff visited each catchment area to collect coordinates of the catchment area boundaries, as these had not been previously captured. The Zimbabwe Census office identified which EAs lay within each catchment area boundary. EAs are selected for inclusion in the survey using the sampling fraction outlined above. In the EAs selected for inclusion, all households are visited and the following screening information is collected from all mothers/caregivers within each household: name, birthdate, whether they are pregnant, if they have any children born in the past 3 years, if they have any children born in the past 3 years that were stillborn or are no longer alive. If mothers/caregivers have a child born in the past 3 years (alive or deceased), the name and birthdate of each child are recorded. Staff will utilize GPS coordinates collected from all households to revisit eligible households at designated dates and times to inform participants that they are selected and therefore invited to participate in the study.

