Secondary outcomes:3)Viral suppression: The proportion of HIV-infected mothers who are virally suppressed 9–18 months postpartum. The denominator (number of HIV-infected mothers) will be assessed as outlined above. The numerator will be assessed based on laboratory viral load test results. Mothers with viral load test results indicating < 1000 copies/ml will be classified as virally suppressed.4)Postpartum engagement in care (among mothers 19–36 months postpartum): The proportion of HIV-infected mothers who were initiated on ART and who continued ART. The denominator (number of HIV-infected mothers who were initiated on ART) will be assessed using: i) laboratory-confirmed HIV test results, or ii) information recorded on maternal health cards, when available, and iii) self-reported ART status. The numerator (number of HIV-infected mothers who were initiated on ART and continued ART after 19–36 months postpartum) will be assessed based on self-reported ART status at the time of the survey. Additionally, we will calculate the average time between delivery and discontinuation of ART among those mothers who did not continue ART.5)Heterogeneity of the impact of Option B+ on HIV-free survival and MTCT by the extent of integration of PMTCT and ART services at health facilities: Impact heterogeneity of Option B+ will be assessed using community-level cross-sectional serosurvey data as well as data on health facility characteristics from the 157 catchment areas selected as PSUs. The extent of integration of PMTCT and ART services at the facility level will be measured using multiple dichotomous variables such as: whether the facility offers both antenatal and labor/delivery services, whether the facility can initiate pregnant women on ART, whether the facility can continue women on ART after a certain number of months after delivery, whether the facility can offer ART services to male partners, and whether the facility can offer ART services to infants and children. Principal component analysis will be employed to estimate the factor loadings of these variables, in order to calculate an overall integration score per facility.6)Incremental cost effectiveness of Option B+: Assessed using effectiveness data (from the community-level cross-sectional serosurveys) along with costing data (from the 157 health facilities surveys). We will estimate the incremental cost-effectiveness ratio (ICER) of option B+ with respect to option A, and the ICER of option B+ with respect to pre-option A guidelines, as the ratio of the difference in costs over the difference in annually-adjusted effectiveness (for each of the two main outcomes: HIV-free infant survival and MTCT).

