Finally, the population-level benefits of Option B+ are predicated on mothers being retained in care for life, and our design will be one of the first population-based assessment of retention in HIV care up to 3 years postpartum among mothers who received Option B+. By simplifying service delivery and reducing the number of steps that mothers need to negotiate, Option B+ is expected to improve retention in care and adherence to ART. Given that the postulated benefits of Option B+ are predicated on HIV-infected mothers staying on ART beyond breastfeeding, our study design will test this assumption.

Our study is subject to limitations. Although our estimates account for transmissions occurring during the first 9–18 months of breastfeeding, HIV-exposed infants may still be breastfeeding at the time of the survey (median duration of breastfeeding is 17.8 months in Zimbabwe) [33]. Estimates of HIV-free survival for 9–18 month old infants may therefore overestimate HIV-free survival at 24 months (at the end of breastfeeding) and may result in an underestimation of MTCT. Nonetheless, estimates restricted to all HIV-exposed infants no longer breastfeeding at the time of our 2012 survey were comparable: 91.9% (95% CI: 86.8–95.1) HIV-free infant survival and 8.1% (95% CI: 4.9–13.2) MTCT [9].

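### The 19–36 month retention outcome pools mothers in a new pregnancy or with a younger baby, so it may overstate staying on ART beyond breastfeeding

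*Protocol article*

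**What the plan says.** All references are to the protocol article.

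- **Purpose.** Sampling strategy gives the reason for the 19–36 month sample: "in order to assess longer term engagement in care following the end of the breastfeeding period". Analyses and Statistical power both describe the quantity of interest as ART continued after weaning. The Discussion notes that the benefits of Option B+ depend on "HIV-infected mothers staying on ART beyond breastfeeding, our study design will test this assumption".
- **Objective.** Specific objectives words Objective 3 more broadly, as retention in ART services at 19–36 months postpartum.
- **Who is eligible.** Study site and population describes an "additional sample of mothers at least 16 years old who have infants 19–36 months of age in order to examine retention in care". It sets no condition on current pregnancy, a later birth or weaning.
- **Numerator.** Study measures, outcome 4, defines it as the "number of HIV-infected mothers who were initiated on ART and continued ART after 19–36 months postpartum", which "will be assessed based on self-reported ART status at the time of the survey".
- **What is recorded.** Community mapping for the endline survey says that the household screen asks mothers "whether they are pregnant, if they have any children born in the past 3 years". Where there is such a child, "the name and birthdate of each child are recorded". The endline questionnaire also asks about ART interruptions.
- **What is done with it.** The only subgroup named for Objective 3 in Analyses is whether the mother was on ART before PMTCT. No section uses the pregnancy item or the later birthdates in the retention outcome.

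**The concern.** The stated question is whether mothers stay on ART once the period of PMTCT and breastfeeding is behind them. By 19–36 months after the index birth some mothers will be pregnant again, and the window leaves room for a second child. Such a mother is in antenatal care or in a new breastfeeding period. Her current ART use belongs to a new PMTCT episode and does not show what happens outside one.

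Limiting the analysis to mothers who have weaned the index child would not remove her. Within this group, a mother who stopped after weaning and restarted because of the new pregnancy is counted as having continued, since the numerator is ART status at one time point.

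What is at stake is the Discussion's claim that the design tests an assumption on which Option B+ depends. If ART use is higher among mothers in a new episode, pooling them moves the estimate towards confirming that assumption.

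**Working it through.** **1. The plan's own figure.** Statistical power gives about 1800 pairs, 11.5% HIV prevalence and about 200 HIV-infected mothers. The refusal rate presumed for the 2017–18 survey is 2%.

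1800 × 0.115 = 207.0, and 207.0 × 0.98 = 202.9. The figure of about 200 reproduces.

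**2. Definition against purpose.** Eligibility rests on the age of the mother and of the index child. The denominator is HIV-infected mothers who started ART, and the numerator is those who report ART now. None of the three depends on whether the mother is outside pregnancy and breastfeeding. The purpose stated in Sampling strategy, Analyses, Statistical power and the Discussion does.

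**3. Possible size.** Let s be the share of ART-initiated mothers in a new pregnancy or with a younger child, R1 current ART use in that group, and R0 current ART use in the others. The pooled proportion exceeds R0 by s × (R1 − R0). The documents give none of these, so all values are assumptions. With R1 = 97%, the shift in percentage points is:

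| R0 | s = 5% | s = 10% | s = 20% | s = 30% |
|---|---|---|---|---|
| 70% | 1.35 | 2.7 | 5.4 | 8.1 |
| 80% | 0.85 | 1.7 | 3.4 | 5.1 |
| 90% | 0.35 | 0.7 | 1.4 | 2.1 |

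A second set, R1 = 95%, gives a similar range:
- s = 10%, R0 = 85%: 0.10 × 0.10 = 1.0 point
- s = 25%, R0 = 75%: 0.25 × 0.20 = 5.0 points
- s = 35%, R0 = 70%: 0.35 × 0.25 = 8.75 points

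**4. Direction.** The shift is upward only if R1 exceeds R0. With R1 = 75%, R0 = 85% and s = 20%, it is 0.20 × (−0.10) = −2.0 points.

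**5. Stop and restart alone.** If a share q of the new-episode group stopped and restarted, counting them as continuing raises the figure by s × q. With s = 5–30% and q = 10–30% (assumed), this runs from 0.05 × 0.10 = 0.5 to 0.30 × 0.30 = 9.0 points. This component can only be upward.

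**6. Precision.** The 95% half-width is 1.96 × √(p(1 − p)/n), with no design effect. Assuming 10–35% of mothers are in a new episode, 180 down to 130 of 200 remain.

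| n | p = 80% | p = 70% |
|---|---|---|
| 200 | 5.5 | 6.4 |
| 180 | 5.8 | 6.7 |
| 130 | 6.9 | 7.9 |

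The shifts in steps 3 and 5 thus run from negligible to larger than the sampling half-width at n = 200.

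**The case against.** The strongest reply is that Objective 3 and the title of outcome 4 ask only about engagement at 19–36 months postpartum, and that Option B+ is lifelong ART. A mother on ART without a break through a later pregnancy is truly retained, and counting her overstates nothing. This stands. She is not misclassified; she is only uninformative about care outside pregnancy and breastfeeding. The pooled figure is a legitimate answer to Objective 3, though not to the question posed in the Discussion.

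A reader might infer that retention is definitely overstated. The documents do not support that. They give no share of mothers in a new pregnancy and no ART use by pregnancy status, and step 4 shows that the net sign can reverse. Only the stop-and-restart component has a known sign, and its size is unknown.

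A reader might also infer that the main estimate should be replaced by one restricted to mothers outside a new episode. That goes too far. The restriction selects on events after the index birth, which may themselves be related to health and engagement in care, and it departs from the wording of Objective 3.

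Two further points stand. Months postpartum in outcome 4 could be counted from the latest birth, which would exclude mothers with a younger baby. Study site and population points to the index child, and the pregnancy part holds on either reading. Also, the pregnancy item is asked at the household screen, before the revisit for interview, so status at the survey may differ.

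One might add that the outcome is secondary and mainly descriptive, that times from delivery and from weaning to stopping ART are also planned, and that further strata belong in an analysis plan. The first two limit the weight of the point. The third does not remove it: the article itself fixes the numerator, the denominator and the conclusion to be drawn, and these do not match.

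**Conclusion.** The point holds in a limited form. As written, outcome 4 does not separate mothers in a new PMTCT episode, and it counts a restart in a new pregnancy as continuation. The pooled proportion therefore cannot by itself carry the Discussion's conclusion about ART beyond breastfeeding, and it may overstate that quantity.

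Size and net direction cannot be derived from the documents. The range of about 0.4 to 9 points upward, or downward if ART use is lower in the new-episode group, rests wholly on assumed shares and ART use. The pooled figure remains valid as ART use at 19–36 months after the index birth. The change is worth making because it is cheap and alters what the study can validly conclude.

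**What to change.** - **Keep** the pooled proportion for Objective 3, labelled as on ART at 19–36 months after the index birth. State that eligibility and time since birth are counted from the index child.
- **Add** to the Objective 3 analysis a split by current pregnancy or a younger child, using the census pregnancy item and children's birthdates. Confirm pregnancy status at interview where the census was earlier.
- **Rest** the Discussion's conclusion about ART beyond breastfeeding on mothers in neither state, and describe them as a descriptive subgroup selected on events after the index birth.

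**Cost.** A change of wording, one extra split in a table and, where the census came earlier, one question at interview. The subgroup is smaller: on the assumed shares, about 130–180 of about 200 HIV-infected mothers, and fewer once limited to those who started ART. Its 95% half-width would be roughly 6 to 8 points before any design effect.
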